#### Sample Size

A total study sample size of 240, with 120 each in the intervention and control arms, was estimated based on the estimates of diastolic blood pressure at baseline (mean 80.9, SD 10.9 mm Hg) and the postintervention time point (mean 75.4, SD 11.5 mm Hg) from a previous randomized controlled trial in Kerala [23]. *OpenEpi* was used for sample size calculation. The sample size was estimated at 80% power, a 95% CI, a 20% nonresponse rate, and a design effect of 1.5.

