#### Sampling

The study followed a multistage cluster sampling method. In the first stage, all taluks in the Kannur district were listed, and then 1 taluk (ie, Payyanur taluk) was selected. One rural (ie, Karivellur-Peralam gram panchayat) and one urban (ie, Payyanur municipality) administrative unit (cluster) from this taluk were then selected for the study (Figure 2). In stage 2, a door-to-door household survey will be conducted in these 2 rural and urban clusters. Household members aged 40 to 59 years will be screened for eligibility after consent is obtained. In the third stage, eligible participants (those with hypertension and access to WhatsApp) will be surveyed. After the baseline survey, the study’s recruitment will follow a nonrandomized approach (Figure 3) without matching or blinding as these are not applicable in this study setting. Upon recruitment and consent, the first participant will be allocated to the intervention group, and the next participant will be allocated to the control group. The participants will be recruited into the intervention and control groups sequentially in a 1:1 ratio. This process will be conducted iteratively until the sample size of 240 is reached (ie, 120 in the intervention group and 120 in the control group). At the cluster level, this amounts to 120 participants per cluster (urban and rural), with 60 of them in the intervention group and 60 in the control group.

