#### Statistical Analysis

The survey data collected will be entered into a Microsoft Excel spreadsheet and then exported to SPSS (version 26; IBM Corp) for coding and analysis. Codebooks and frequency tables will be generated to characterize the responses and identify any data entry errors. The missing data will be characterized as missing at random and missing not at random. The data missing at random will be addressed by creating a new variable or recoding an existing variable to account for the missing response. The data missing not at random will be addressed using the last observation carried forward approach (if the missing data were due to loss to follow-up) or regression imputation. Case deletion will be used if there are any missing data observed in multiple outcome variables. The analysis will be conducted adhering to the intention-to-treat approach. Study variables will be developed based on the operationalization plan shown in Table 1.

Descriptive analyses, including frequencies and percentages for categorical variables and means and SDs for continuous variables, will be conducted to understand the sample characteristics. The sociodemographic and health-related characteristics of the intervention and control groups will be compared at baseline. Furthermore, the outcome variables, including medication and lifestyle factors, will be compared between and within the intervention and control groups using baseline and follow-up data.

The comparison of categorical outcomes (medication and lifestyle factors) between and within the intervention and control groups will be conducted using the chi-square test and logistic regression. The regression analysis will be reported as unadjusted odds ratios with 95% CIs. The comparison of continuous outcomes (waist-to-hip ratio, awareness of hypertension, medication adherence score, and duration of physical activity) between the intervention and control groups will be conducted using a 2-tailed independent-sample *t* test (for normally distributed data) and the Mann-Whitney *U* test (for nonnormally distributed data). For comparisons of continuous outcomes within the intervention and control groups, a paired *t* test (for normally distributed data) and a Wilcoxon signed-rank test (for nonnormally distributed data) will be used.

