The generalized estimating equations model will be used to assess the effectiveness of the mHealth intervention based on the longitudinal study data (data from the baseline and follow-up surveys). Variables such as time, intervention, time-intervention interaction, and other sociodemographic factors will be considered in the model. The analysis using the generalized estimating equations model will be presented as adjusted odds ratios with 95% CIs. The significance will be considered at a *P* value of less than .05.

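### Allocation is fixed at 60:60 within the rural and the urban unit, but the simple between-arm comparisons ignore the unit and the GEE does not commit to it: a small, conditional loss of power that is free to avoid

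*Protocol article*

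**What the plan says.** **Allocation (Sampling).** One rural and one urban administrative unit are chosen from one taluk. "The participants will be recruited into the intervention and control groups sequentially in a 1:1 ratio", by alternation and without randomization. The split is held within each unit: "this amounts to 120 participants per cluster (urban and rural), with 60 of them in the intervention group and 60 in the control group".

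**Sample size (Sample Size).** The calculation allows for "a 20% nonresponse rate, and a design effect of 1.5". The Discussion also says that the cluster effect was allowed for in the sample size.

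**Simple comparisons (Statistical Analysis).** Categorical outcomes compared "between and within the intervention and control groups will be conducted using the chi-square test and logistic regression". For the regression: "The regression analysis will be reported as unadjusted odds ratios with 95% CIs". Continuous outcomes are compared between arms by the independent-sample t test or Mann-Whitney U. The unit appears in none of these.

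**Effectiveness model (Statistical Analysis).** A GEE on baseline and follow-up data is the model named for assessing effectiveness, and it is reported as adjusted odds ratios. Its covariates are described thus: "Variables such as time, intervention, time-intervention interaction, and other sociodemographic factors will be considered in the model". Table 1 lists residence among the sociodemographic characteristics.

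**The concern.** A factor within which the arm split is fixed is a stratum of the design, and the analysis should normally use it. When the arms are balanced within units and the outcome level differs between units, leaving the unit out has two consequences. Between-unit variation goes into the variance of the simple tests, although balance has already removed it from the arm comparison, so the tests reject too rarely. And a logistic model without the unit estimates a marginal odds ratio, which lies nearer 1 than the within-unit odds ratio.

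Diet, physical activity and adherence could plausibly differ between a gram panchayat and a municipality. The plan enlarges its sample by half on account of area clusters and then names no analysis in which the area is certain to appear. What is at stake is some power and clarity about which odds ratio is reported. The false-positive rate is not at risk from this source.

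**Working it through.** **1. The plan's own sample size.** Inputs from Sample Size: diastolic pressure 80.9 (SD 10.9) and 75.4 (SD 11.5) mm Hg, difference 5.5, 80% power, two-sided 5%.

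n per arm = (10.9² + 11.5²)(1.96 + 0.842)² / 5.5² = 65.1, rounded up to 66. Then 66 × 1.5 = 99, and 99 × 1.2 = 118.8, or 119, against the stated 120. The figure reproduces, and the factor of 1.5 is in it.

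**2. Assumptions for the binary outcomes.** The article gives no outcome figures by unit, so control prevalences in the two units are assumed over a range. The within-unit odds ratio is taken as 2.0 in both units. All 60 per arm per unit are analysed, and alternation is treated as if it made the arms comparable within unit.

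**3. Type I error of the plain chi-square.** The variance used by the test is p̄(1 − p̄), with p̄ the mean prevalence. The variance that applies under balance within unit is the mean of pᵢ(1 − pᵢ). The SE ratio r is the square root of the first over the second, and actual type I error is 2[1 − Φ(1.96 r)].

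- 40%/60%: √(0.2500/0.2400) = 1.021
- 30%/60%: √(0.2475/0.2250) = 1.049
- 25%/65%: √(0.2475/0.2075) = 1.092

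**4. Marginal odds ratio.** Apply an odds ratio of 2.0 in each unit, average the prevalences over units, and form the odds ratio of the averages. For 25%/65%, the intervention prevalences are 40.0% and 78.8%, mean 59.4%. The control mean is 45%. The marginal odds ratio is (0.594/0.406)/(0.45/0.55) = 1.79.

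**5. Power.** Φ((d − 1.96·SE₀)/SE₁), where d is the difference in mean prevalence. SE₀ is the null standard error, without or with stratification by unit. SE₁ is the sampling standard error under balance within unit.

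| Control prevalence in the two units | SE ratio | Actual type I error | Unadjusted OR (within-unit 2.0) | Power, unit ignored | Power, stratified |
|---|---|---|---|---|---|
| 50% / 50% | 1.000 | 5.0% | 2.00 | 74.8% | 74.8% |
| 40% / 60% | 1.021 | 4.6% | 1.95 | 71.9% | 73.2% |
| 30% / 60% | 1.049 | 4.0% | 1.88 | 68.6% | 71.8% |
| 25% / 65% | 1.092 | 3.2% | 1.79 | 61.8% | 68.3% |

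**6. Standard error of the log odds ratio.** At 30%/70% with within-unit odds ratio 2.0, the unadjusted model gives an SE of 0.264 and the unit-adjusted model 0.289. Adjustment does not narrow it. The gain is in the test: ln(1.797)/0.264 = 2.22 unadjusted against ln(2.0)/0.289 = 2.40 adjusted.

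**7. Continuous outcomes, illustration only.** With 11.2 mm Hg as the within-unit SD and a difference D between units, the SE is inflated by √(1 + (D²/4)/11.2²): 1.025 at 5 mm Hg and 1.062 at 8 mm Hg. If 11.2 is taken as the total SD, the factors are 1.026 and 1.071. Blood pressure is not in the article's list of outcomes for the t test, so these figures only show the scale of the effect.

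**The case against.** The strongest reply is that the effectiveness analysis is the GEE and not the simple comparisons. Residence belongs to the class of covariates that the GEE may include, and a final covariate list is commonly left to an analysis plan. For a continuous outcome, the time-by-intervention term compares changes, so a constant rural-urban gap in level largely cancels even if residence is left out. All of this stands. It limits the point to the simple comparisons and to the missing commitment in the GEE, and the figures above do not carry over to the GEE.

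The effect is also hypothetical and, for modest differences, small. That stands too. The sample has slack as well: on the plan's diastolic inputs, 96 completers per arm (120 less 20%) give about 92.5% power in a simple comparison.

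Three stronger readings are tempting, and the document supports none of them.

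- *The unadjusted odds ratios are biased.* With arms balanced within units, the shift toward 1 is non-collapsibility. The marginal odds ratio is a legitimate quantity.
- *All the reported intervals are too wide.* Step 6 shows that the adjusted log odds ratio has the larger standard error. Excess width applies to mean differences and to the null variance of the chi-square.
- *The design effect of 1.5 shows that ignoring the units inflates false positives.* Both arms are present in equal numbers in each unit, so the error goes the other way.

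Nor can it be said that results by unit are excluded. The article is silent on them, and silence is no finding here.

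**Conclusion.** The point holds as a low-severity improvement. The article states the simple tests and the unadjusted odds ratios affirmatively, and they do not use the factor within which the 60:60 split is fixed. The GEE leaves inclusion of that factor open.

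The loss depends wholly on a rural-urban difference in outcome that the document does not give. It is zero without one, about 1 power point at 40%/60% and about 6 points at 25%/65%, always in the conservative direction. These figures assume a within-unit odds ratio of 2.0 and 60 analysed per arm per unit. Dropout would lower both power columns and make the balance only approximate. The nonrandomized allocation is a separate matter that stratifying by unit does not resolve.

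**What to change.** State in the analysis section that:

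- unit (rural or urban) is a fixed covariate in the GEE;
- unit is a fixed covariate in the between-arm linear and logistic models, which replace the plain t test and the unadjusted odds ratio as the main between-arm summaries;
- the Cochran-Mantel-Haenszel test stratified by unit replaces the plain chi-square between arms;
- the two units are not used as GEE clusters, because two clusters cannot support a robust variance. The participant remains the cluster for the repeated measurements.

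If unadjusted odds ratios are kept alongside, label them as marginal. A unit-by-time term in the GEE and estimates by unit with 95% CIs are optional. With 60 per arm such estimates are imprecise, so they should be descriptive and not separate tests.

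The cost is analysis wording and one degree of freedom, or two with the optional term. The unit is known for every participant. Data collection is complete and analysis is planned to run to April 2026, so the change should be dated and recorded as made before the arms are compared, if that is still the case.

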**Figure 2. F2:**
[figure not shown]
Study location in the Kannur district of Kerala, India. Source: Wikimedia Commons (2023).

**Figure 3. F3:**
[figure not shown]
Transparent Reporting of Evaluations With Nonrandomized Designs (TREND) statement flow diagram of the study. DBP: diastolic blood pressure; mHealth: mobile health; SBP: systolic blood pressure.

#### Standard Hypertension Care

All participants will be advised to follow the consulting physician’s advice, continue medication, maintain regular blood pressure monitoring, and attend health care visits. Participants will receive health education, including the importance of healthy eating with controlled salt intake and adequate fruit and vegetable intake; regular physical activity; proper medication; and avoiding unhealthy behaviors such as alcohol consumption, tobacco use, and processed food intake. Participants will be reminded about the follow-up survey, which will be conducted 3 months after the baseline survey.

#### Intervention*:* WhatsApp-Led mHealth Strategy

A WhatsApp-led mHealth strategy was developed (Figure 4) with participant-specific messages and posters, which were prepared based on standard hypertension management protocols [24-28]. WhatsApp, an instant messaging platform owned by technology conglomerate Meta Platforms, was chosen due to its universal adoption and ease of use and the possibility of sending health messages through text and multimedia (image, voice, and video) formats. The intervention duration was determined to be 3 months based on the review period for hypertension as per the hypertension management protocol of the Department of Health Services, Government of Kerala [12,24].

**Figure 4. F4:**
[figure not shown]
WhatsApp-led mobile health intervention for medication and lifestyle adherence in participants with hypertension.

The diagnosis and treatment details of the study participants will be obtained during the baseline survey. Furthermore, the messages will be tailored considering their hypertension treatment status (ie, those who are under medication and those who are not under medication). Among those who are under medication, awareness of healthy lifestyles will be promoted, and they will receive reminders for proper medication adherence, regular consultation with their treating physician, and blood pressure monitoring. Newly diagnosed individuals with hypertension and those who are not in treatment will be sent health messages highlighting the need to adhere to positive health behaviors, consult a physician, and monitor their blood pressure periodically.

The messages for a healthy lifestyle include awareness and reminder messages for keeping healthy eating habits, focusing on the Dietary Approaches to Stop Hypertension diet. The messages also include the need for adequate physical activity and a list of physical activities classified by effort level (mild, moderate, and vigorous). Messages on the importance of reducing mental stress, quitting smoking, avoiding exposure to secondhand smoke, and controlling alcohol intake will also be shared with the participants.

Participants in the intervention group will be advised to follow standard hypertension care. Additionally, participants will be invited to join the intervention through an invitation message and will be listed to receive personalized hypertension management messages via WhatsApp (Figures5  6). The health messages and posters will be shared in the morning at around 6 to 7 AM. Messaging will start within a month following the baseline survey. The intervention will continue from that day for the next 90 days. In the first month (first 30 days), messages will be shared daily; in the second month (middle 30 days), messages will be shared twice a week; and in the third month (last 30 days), messages will be shared once a week (7 days). There will not be a specific day of the week to send messages; days will be calculated from the first day that participants start receiving messages, not from the beginning of a month or a week. The messages will be shared in the participants’ preferred language (English or Malayalam), and their responses will be documented to check for participant engagement. The follow-up survey will be conducted after 3 months at the end of the intervention period. Participant engagement with the intervention will be actively monitored throughout the intervention period. A total of four steps will be followed as part of the audit trail to ensure that the messages are seen by the participants: (1) highlighted tick marks for each message shared with the participants, (2) message viewing status from the message information option on WhatsApp, (3) any response (in the form of a like or emoji) or comment from the participants after receiving the message or poster that was shared with them, and (4) monthly confirmation through phone call or home visit to ensure that the participants are receiving the messages. Any instances of disengagement from the participants will be noted and followed up on (through WhatsApp messaging, home visit, or phone call) by the principal investigator to reinforce the importance of being actively involved in the study and address any concerns.

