**Figure 6. F6:**
[figure not shown]
Participant-specific health messages related to healthy lifestyle and medication. (A) Translation of the messages from the chat page of Intervention PDM 7 (a physician-diagnosed participant with hypertension taking antihypertensive medication): “1) Include vegetables, fruits, and whole grains in the diet; 2) The practice of regular physical activities helps to control hypertension, so, fix a time for exercise in the morning or evening; 3) This is a reminder to take your anti-hypertensive medication on time. Try to have an appointment with your consulting doctor at least once every 4 weeks.” (B) Translation of the messages from the chat page of Intervention CS 3 (hypertension case found during screening): “Measures to control hypertension—practice exercise daily (at least 150 minutes a week), include fruits and vegetables in the diet (take at least 4-5 servings a day), restrict excess salt intake (consume only less than 5 gm), stop using tobacco, and control consuming alcohol” (from the poster) and “It is important to reduce mental stress to control hypertension” (from the message).

Participants in the control group will be advised to continue standard hypertension care and reminded of the follow-up survey 3 months after the baseline survey. To ensure that the participants in the control group also benefit from being part of the study, they will receive the messages and posters after the follow-up survey.

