## Results

All 240 participants were recruited by July 2025. The study completed data collection in August 2025 and is expected to finish data analysis by April 2026. The study results are expected to be submitted for publication in July 2026. The baseline survey will help understand the participant characteristics, medication status, lifestyle factors, and blood pressure measurements before the intervention. The intention to use the mHealth strategy for hypertension management is also measured at this stage. The follow-up survey data will provide the participant characteristics after the intervention phase. The baseline and follow-up survey data will allow us to study the effectiveness of the intervention on the medication and lifestyle variables. Furthermore, the in-depth interviews will help provide insights into the lived experiences of participants during the period of the intervention, focusing on the adaptation of the mHealth intervention for adherence to medication and a healthy lifestyle. The interviews will also enable the understanding of the perceived effectiveness of the intervention. The study has not received any funding.

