The follow-up survey time point of 3 months after the intervention was determined based on the review period (ie, 3 months) for lifestyle and blood pressure measurement changes as per the hypertension management protocol of the Department of Health Services, Government of Kerala [24]. This duration of 3 months is also based on the minimum period required for behavior changes or to develop new habits, including physical activity and dietary changes [12,44,45]. The long-term sustainability of behavior change and the durability of the mHealth intervention will be explored through the qualitative interviews. Even though the intervention ends after 3 months, the ability to keep the messages for an indefinite time, as well as the option to create a backup in WhatsApp, allows the participants to go through the messages again if needed after the intervention period.

WhatsApp is a ubiquitous platform that is not primarily meant for medical communication. However, given the real-time nature of WhatsApp-based intervention and health messaging specific to the individual participant, this study is expected to be effective in improving adherence to medication and healthy lifestyle and have better participant engagement with the mHealth intervention.

The individualized delivery method, with a person-to-person (researcher-to-participant) messaging system rather than a WhatsApp group or community, will help minimize contamination between the intervention and control groups. Additionally, all participants will be recruited from their homes and monitored regularly during the follow-up period until the end-line survey. In addition, during sample size estimation, the researcher accounted for the cluster effect to obtain an adequate sample size to prevent the reduction in the samples’ power due to contamination.

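### The follow-up survey is set at two different times: 3 months after baseline, and the end of 90 days of messaging that starts up to a month after baseline

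*Protocol article*

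**What the plan says.** The protocol article gives the timing of the follow-up survey in several places.

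- **Standard Hypertension Care** (addressed to all participants): "Participants will be reminded about the follow-up survey, which will be conducted 3 months after the baseline survey".
- **Intervention: WhatsApp-Led mHealth Strategy**, on when messaging runs: "Messaging will start within a month following the baseline survey. The intervention will continue from that day for the next 90 days". The day count starts at each participant's first message. On the survey, the same section says: "The follow-up survey will be conducted after 3 months at the end of the intervention period". The abstract also puts the survey at the end of the intervention.
- **Control-group paragraph** at the end of the intervention section: controls are "reminded of the follow-up survey 3 months after the baseline survey".
- **Discussion, Expected Findings**: "The follow-up survey time point of 3 months after the intervention". The same section describes four batches of about 30 participants per arm, used to shorten the gap between baseline and the first day of messaging.
- **Results**: "All 240 participants were recruited by July 2025. The study completed data collection in August 2025".

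The effectiveness analysis (Statistical Analysis) is a generalized estimating equations model on the baseline and follow-up surveys, with time, intervention and their interaction among the terms named.

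**The concern.** The two definitions start from different days. One counts from the baseline survey. The other counts from the first message, which may come up to a month later. The batching text confirms that a gap is expected: it says the gap is to be reduced, not that it is removed. Nothing ties a control participant's survey date to the end of messaging in the same batch.

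What is at stake is when the primary outcomes (blood pressure and adherence to medication and lifestyle) are measured. If each arm follows its own text, the intervention arm has a longer interval. Any change during the extra days, such as season, medication changes, or newly detected participants starting treatment, then enters the time-by-intervention term. If everyone is surveyed 3 months after baseline, the elapsed time is equal, but participants whose messaging started late are measured before their course ends. Allocation is nonrandomized and unblinded, so a further avoidable difference between arms is unwelcome.

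**Working it through.** **Inputs, all from the protocol article.** Lag from baseline to first message: 0 to about 30 days (intervention section). Length of messaging: 90 days from the first message (same section). Survey for controls and, under Standard Hypertension Care, for everyone: 3 months after baseline, taken here as about 90 days. The sample size of 240 does not enter the argument.

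**Step 1. Interval if each arm follows its own text.** Intervention: lag + 90. Control: about 90.

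| Lag (days) | Intervention survey (day) | Control survey (day) | Excess (days) | Excess / 90 |
|---|---|---|---|---|
| 0 | 90 | 90 | 0 | 0% |
| 15 | 105 | 90 | 15 | 17% |
| 30 | 120 | 90 | 30 | 33% |

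The excess is never negative, so it does not average out across participants. The distribution of the lag is not given; 15 days is only a midpoint.

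**Step 2. Exposure if everyone is surveyed at about day 90.** Days of messaging delivered = 90 − lag, so 60 to 90 of the 90 planned.

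**Step 3. Messages missing in that case.** The schedule is daily for 30 days, twice a week for 30 days, then weekly for 30 days:

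- first 30 days: 30
- middle 30 days: 2 × 30/7 = 8.6
- last 30 days: 30/7 = 4.3
- total: 30 + 8.6 + 4.3 = 42.9, about 43

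With the full 30-day lag the last 30 days are lost: 4.3/42.9 = 10% of messages. One third of the duration is therefore about one tenth of the content.

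**Step 4. Consistency.** Lag + 90 equals 90 only when the lag is 0. The baseline-based and messaging-based definitions therefore cannot both hold for anyone whose messaging starts later than the baseline day.

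**Step 5. Calendar dates (supporting only).** Counting back from 31 August 2025, the last day on which data collection could have ended:

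- 31 August − 90 days = 2 June 2025, the latest baseline for a 90-day follow-up
- 31 August − 120 days = 3 May 2025, the latest baseline with a 30-day lag

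**Step 6. Size in mm Hg.** The documents give no rate of change over time. For scale only, an assumed drift of 0.5 to 2 mm Hg per month gives 0.5 to 2 mm Hg if every lag is 30 days, and 0.25 to 1 mm Hg at a mean lag of 15 days. This is an illustration, not an estimate.

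**The case against.** A reader might infer that the design confounds arm with elapsed time. The text does not support that as a settled fact. Standard Hypertension Care gives one clock for all participants, and under it the arms share the same interval. Arm-specific clocks are one of two readings. What stands is that the article states both.

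The magnitude can also be overread.

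- The batches exist to shorten the gap, so 30 days is an upper limit rather than a typical value.
- The 5.5 mm Hg difference behind the sample size (80.9 − 75.4) is a before-and-after difference from a cited trial. It is not stated as a planned between-arm effect, so it is a poor yardstick for the drift in step 6.
- Participants alternate between arms and each batch contains both, so batch effects are not aligned with arm, and calendar period differs between arms only by the lag.
- Regression to the mean affects both arms, and nothing shows that it would differ materially between day 90 and day 120.

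Two supporting points are weaker than they look. A reader might infer from the Results dates that participants enrolled in July were followed up for a month or less. The text sets July 2025 as an outer bound for recruitment and does not say that anyone enrolled that month; a date problem would also not by itself separate the arms. The Discussion wording, read literally, would put the survey 3 months beyond the end of messaging. It is probably loose phrasing, since the same section ties the time point to a 3-month review period.

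Finally, how time is coded in the model may properly be left to an analysis plan that is not shown. That is fair, and the point does not depend on it. The conflict over when the survey takes place is in the article itself.

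**Conclusion.** The point holds as an inconsistency in the timing of the primary outcome measurement. Followed as written, the plan leads to one of two results:

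- the intervention arm is measured 0 to 30 days (0% to 33%) later than controls, always in the same direction; or
- it is measured at about day 90 with 60 to 90 of the 90 days delivered, and at most about 4 of roughly 43 messages missing.

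This rests on 3 months being about 90 days and on the stated limit of one month for the lag. The article does not establish which reading was applied, how the lag was distributed, or the direction and size of any bias in blood pressure or adherence. The calendar dates and the Discussion wording only support the request for clarification. The matter should be settled before the analysis is finished, which the article expects by April 2026.

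**What to change.** 1. Reconcile Standard Hypertension Care, the intervention section, the control-group paragraph and the Discussion to one index date shared by both arms. One option is the start of messaging in a batch, applied to intervention and control participants of that batch. Data collection is reported complete, so a common survey window can no longer be imposed; the text should say which rule was actually applied.
2. Report the actual days from baseline to follow-up by arm and batch, and the days from first message to follow-up for the intervention arm by batch.
3. Include batch in the outcome model. This accounts for differences between batches; it does not remove an offset between arms within a batch, which is why items 2 and 4 matter more.
4. Add a sensitivity analysis restricted to the range of baseline-to-follow-up intervals found in both arms.
5. Treat adjustment for the interval as secondary only. If controls cluster near day 90 and intervention participants spread to day 120, interval is nearly collinear with arm and the adjusted estimate relies on extrapolation.
6. Clarify the July and August 2025 dates, for example by giving the dates of the last baseline survey and the last follow-up survey.

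The cost is wording, one model term and one extra analysis, using survey and first-message dates that should already be in the study records. The main downside is in item 4: if lags were common, the restricted analysis may lose a sizeable share of the intervention participants whose messaging started late, with a loss of precision and a more selected group.
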